### Overview of study design

This study is a single-center, open-label, randomly-allocated cohort study, with CKD patients in stages G2, G3a and G3b. To reduce the risk of sampling error, the enrolled patients will be randomly assigned based on the stratified random sampling process by using the random sequence generated by a computer software [22, 23]. The used variables for the stratification will be age (i.e. ≥65, < 65 years old), sex, presence of diabetes mellitus, and eGFR (i.e. ≥46, < 46 ml/min/1.73m^2^). With these four variables, the enrolled patients will be divided into 16 subgroups, and then randomly allocated into the below-described three cohort groups from each of the subgroups.

The enrolled patients will be allocated into the following three cohort groups: 1) sodium bicarbonate group, 2) sodium-potassium citrate group, and 3) standard therapy group without any alkalinizing agents. Then, these three cohort groups will be measured for the targeted biomarkers in the serum and urine in the “short-term” study (i.e. at 0, 6, 12 and 24 weeks after starting the intervention) and in the “long-term” study (i.e. at 1 and 2 years after starting the interventions) to assess the effects of oral alkalinizing agents. As for the urine samples, both early-morning urine and spot urine will be collected. The above-described overview of this cohort study is shown in Fig. 1.

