### Endpoints

The primary endpoints will be **1)** the development of significant renal dysfunction, **2)** the occurrence of any kind of cerebrovascular disease between 0 and 24 weeks (short-term study) from starting the interventions. The significant renal dysfunction will be defined as the conditions that fulfill at least one of the following four criteria; 1. serum Cre level ≥ 1.5 times higher than that at 0 week, 2. eGFR decrease ≥20 ml/min/1.73m^2^ from that at 0 week, 3. proteinuria ≥3.5 g/gCr, 4. new development of urinary stones. The secondary endpoints will be the above-described criteria at 1 and 2 years (long-term study) from starting the interventions, and finding any kind of reno-protective marker associated with alkalinizing agents in both periods of study (Table 3).

**Table 3 Tab3:** Primary and Secondary Endpoints

Endpoints	Period	
Primary	Short-term	1) The development of significant renal dysfunction 1. serum Cre level ≥ 1.5 times higher than that at 0 week 2. eGFR decrease ≥20 ml/min/1.73m^2^ from that at 0 week 3. proteinuria ≥3.5 g/gCr 4. new development of urinary stones 2) The occurrence of any kind of CVD and the death
Secondary	Lon-term	1) The development of significant renal dysfunction 2) The occurrence of any kind of CVD and the death
	Short-term & Lon-term	Reno-protective marker associated with alkalinizing agents in both periods of study, for example, category II (blood tests), categoryII (urine test), urine pH and unknown surrogate biomarkers of early renal damage, including uremic toxins and known metabolites measured by metabolomics.

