## Discussion

Recruitment to this cohort study terminated in March, 2018, and the follow-up period for all the enrolled subjects will be terminated in December, 2020.

We will seek for new therapeutic strategies using oral alkalinizing agents for the early stage CKD patients in this CKOALA study. Based on the previous study that showed the reno-protective effects of the oral sodium bicarbonate in the animal CKD model [17], we hypothesized that administration of oral alkalinizing agents for the patients with mild and moderate stages of CKD would delay the development of ESKD. This cohort study will confirm the reported benefits of oral alkalinizing agents for suppressing CKD progression in actual human cases.

In addition to the expectation that this study will confirm the therapeutic effects of oral alkalinizing agents for CKD patients, it would also clarify the relationship between the urine pH and the chronic renal damage. Because the oral alkalinizing agents have been suggested to only alkalize the urine without changing serum pH, if the reno-protective effects of oral alkalinizing agents are confirmed, it will strongly suggest that aciduria is a definite risk factor to promote the renal damage in CKD patients.

One of the strengths of this study is that it will be conducted in a single center, which will enable us to exclude the risks of biases based on the differences between facilities and examiners. Meanwhile, there are some limitations. First, the number of enrolled subjects may remain low. If the results become negative due to inadequate sample size, we may extend the study period or plan additional randomized multi-center cohort study to achieve an adequate sample size. Another limitation is that this study will be an open-label trial. However, because the endpoints of this study are comprised of objectively measured serum and urine biomarkers that could not be affected by the preconceptions, biases based on the open-label style of this study to the given endpoints are not likely. Lastly, as for the patients’ compliance to the medications, we will interview the intake habit at all the occasions of their hospital visits.

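### The reason given for discounting open-label bias fits three laboratory criteria but not urinary stones or vascular events, which are also part of the primary endpoint

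*Protocol article*

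**What the plan says.** The Overview of study design states: "This study is a single-center, open-label, randomly-allocated cohort study". The control arm receives standard therapy without an alkalinizing agent.

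The limitations paragraph of the Discussion names the open-label design as a limitation and then sets it aside "because the endpoints of this study are comprised of objectively measured serum and urine biomarkers that could not be affected by the preconceptions". From this it concludes that "biases based on the open-label style of this study to the given endpoints are not likely".

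The Endpoints section defines the primary endpoint in two parts:

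- **Significant renal dysfunction.** Any one of four criteria is enough. Three are laboratory values: creatinine, eGFR and proteinuria. The last is "4. new development of urinary stones".
- **Vascular events.** The text has "the occurrence of any kind of cerebrovascular disease between 0 and 24 weeks". Table 3 words this part as "The occurrence of any kind of CVD and the death".

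The same criteria are secondary endpoints at 1 and 2 years.

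**The concern.** The dismissal rests on a premise about what the endpoints are, and the document's own endpoint definition does not meet it. A stone or a vascular event enters the data only if someone looks for it and classifies what is found. Where the arm is known, both steps can differ between arms. A laboratory value, once the sample is drawn, is much less exposed.

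At stake is how a difference on the primary endpoint may be read. If it came mainly from stones or vascular diagnoses, unequal ascertainment would be a possible explanation, and the limitations paragraph would give the reader no warning of it. A conclusion about renal function would then rest on components that do not measure renal function.

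**Working it through.** **1. Premise against definition.** No figure is needed here. Each component is compared with the description "the endpoints of this study are comprised of objectively measured serum and urine biomarkers".

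| Component (Endpoints, Table 3) | Serum or urine measurement? |
|---|---|
| Creatinine at least 1.5 times the week-0 value | Yes |
| eGFR fall of at least 20 ml/min/1.73m² | Yes |
| Proteinuria of at least 3.5 g/gCr | Yes |
| New urinary stones | No |
| Cerebrovascular disease (Table 3: CVD), any kind | No |
| Death (Table 3 only) | No, but hardly open to interpretation |

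The premise covers three of the four renal criteria and none of the second part. Because one criterion suffices, a stone alone makes a case.

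**2. What the article says on ascertainment.** It gives no diagnostic definition of stones or vascular disease and does not say who assesses them. Table 1 schedules renal ultrasound for all patients at 0 and 24 weeks and at 1 and 2 years. The items that Collected variables names for that scan are intrarenal blood flow and renal size; stones are not among them.

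**3. Illustration of size.** The documents give no figure to reproduce on this point. Inputs:

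- n = 50 per arm (Sample size calculation).
- Significance level 0.05 (Sample size calculation), and 0.01 (the threshold in Analysis).
- True event rate 5% in every arm: an assumption. The 5% and 30% in the sample size section are ESKD rates, not rates of this endpoint.
- Excess detection d in one arm: an assumption.

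Let X ~ Bin(50, 0.05) and Y ~ Bin(50, 0.05 + d). The false-positive rate is the sum of P(X = x)·P(Y = y) over all pairs (x, y) whose two-sided Fisher p-value is below the level.

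| d | Expected extra diagnoses (50 × d) | At 0.05 | At 0.01 |
|---|---|---|---|
| 0 | 0 | 0.7% | 0.06% |
| 0.04 | 2 | 4.3% | 0.9% |
| 0.06 | 3 | 8.9% | 2.5% |
| 0.10 | 5 | 24% | 10% |

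With two extra diagnoses the rate stays below the nominal level at both thresholds. It exceeds nominal from about three. The 0.7% in the first row is low because Fisher's test is conservative at such rates, so the nominal level is the fairer comparison.

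**4. Is a laboratory-only version available?** Serum creatinine and eGFR (blood category I) and urine protein and creatinine (urine category I) are collected at every visit in Tables 1 and 2. Criteria 1 to 3 can therefore be computed without new data.

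**The case against.** The strongest reply is that this is one imprecise sentence in a paragraph that openly lists open-label design as a limitation. Most of the renal definition is laboratory-based. Ultrasound follows the same schedule in every arm. Masked adjudication may be described in the full protocol, which is not shown. Supportive composites and component counts are usual SAP content.

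Much of this stands. The common ultrasound schedule partly equalises stone detection, though only partly, since stones are not a named item of the scan. The absence of an adjudication procedure from the article is not the finding. Even if one exists, the reason printed in the Discussion would still be wrong for two components of the primary endpoint.

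A reader might infer more than the document supports:

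- *That these events are diagnosed by staff who know the arm.* The article does not say who assesses them or how.
- *That the text rules bias out.* It calls bias unlikely; the stronger phrase about preconceptions describes the biomarkers, for which it is largely fair.
- *That any bias would favour the alkali arms.* The direction is not established. The treated arms have dose adjustment driven by urine pH, and closer attention there could raise detection in those arms instead.
- *That a laboratory-only result would be free of open-label bias.* Censoring criteria exclude the data of censored subjects, and the reasons include adverse events and withdrawal. Those decisions can depend on the arm and would affect criteria 1 to 3 as well.

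**Conclusion.** The point holds in a limited form. The justification in the Discussion is sound for the measurement of creatinine, eGFR and proteinuria. It does not hold for "new development of urinary stones" or for cerebrovascular disease/CVD of any kind, whose ascertainment the article leaves unstated. This rests on the text alone and depends on no number.

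The false-positive rates show only that a small imbalance in diagnoses could matter. They rest on an assumed 5% rate and an assumed excess, and they pass the nominal level only from about three extra diagnoses per 50 patients. They are not an estimate of bias in this trial. The correction leaves the endpoint definition and the planned tests unchanged, but it does affect what may be concluded about renal function.

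**What to change.** 1. In the Discussion, limit the statement to the measurement of criteria 1 to 3, and add that stones and vascular events may be subject to ascertainment bias because treatment is open-label. Suggested wording: 'Criteria 1 to 3 are laboratory measurements and their determination is unlikely to be influenced by knowledge of the arm. Detection and classification of urinary stones and vascular events may be.'
2. Before outcomes are compared by arm, specify a supportive laboratory-only composite (criteria 1 to 3), reported beside the full endpoint, with counts by arm for every component, including death.
3. Do not present the laboratory-only result as free of open-label bias; refer to the exclusion of censored subjects' data.

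Cost: a change of wording, one extra table, and a slightly less favourable claim. No new data, staff or procedures are needed.

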## Data Availability

We informed the possibility that the samples and analysis results could be provided to other research institutes for secondary use, but personally identified information should not be used. The data that support the findings of this study are available from the Data center of Clinical Research, Innovation and Education Center (CRIETO) of Tohoku University Hospital, but restrictions apply to the availability of these data, which were used under license for the current study, and so are not publicly available. Data are however available from the authors upon reasonable request and with permission of the Data center of CRIETO.

## Abbreviations

CKD: Chronic kidney disease
ESRD: End-stage kidney disease
QOL: Quality of life
UT: Uremic toxins
ABI: Ankle brachial index
CAVI: Cardio ankle vascular index
ECG: Electrocardiogram
US: Ultrasonography
eGFR: Estimated glomerular filtration rate
LDL: Low-density lipoprotein
HDL: High-density lipoprotein
CRP: C-reactive protein
BUN: Blood urea nitrogen
TIBC: Total iron binding capacity
UIBC: Unsaturated iron binding capacity
AST: Aspartate transaminase
ALT: Alanine transaminase
LDH: Lactate dehydrogenase
ALP: Alkaline phosphatase
PTH: Parathyroid hormone
BNP: B-type natriuretic peptide
BAP: Bone specific alkaline phosphatase
ACTH: Adrenocorticotropic hormone
ET-1: Endothelin-1
RBP: Retino-binding protein
NGAL: Neutrophil gelatinase-associated lipocalin
KIM-1: Kidney injury molecule 1
L-FABP: Liver-type fatty acid-binding protein
MCP-1: Monocyte chemotactic protein-1
IL-1β: Interleukin-1β
IL-6: Interleukin-6
TNF-α: Tumor necrosis factor-α
CKOALA: Estimating the efficacy of the oral alkalinizing agents in CKD
